### Eligibility criteria

#### Inclusion criteria

NHS patients, with burn injuries >1% Total Body Surface Area, are eligible if they have been treated with skin grafts or had conservatively managed burn wounds or donor sites that:

have delayed healing of greater than 14 days.have potential for hypertrophic scarring.are suitable for scar management therapy.

The scar must be within 3 months of healing, where healing time-point is defined by the Healthcare Professional (HCP) during wound management. This time to healing must be for the study scar that is included in the study. The combination of excessive redness with increased thickness and/or hardness provides clear indication of potential scarring, as defined by HCP assessing for scar management.

Where there are multiple scars, the scar having the greatest impact, as reported by the patient, will be included in the trial. Only one scar per patient will be included, and this scar will be identified prior to randomisation. No other scars will be treated with laser until after the study ends for the participant (i.e. post week 26 visit).

The approximate size of the study scar would be anything up to 200 cm^
2
^. The size or extent of laser treatment would be determined by or in discussion with the laser operator. The minimum size for the study scar would be 4 cm × 4 cm. The latter is the size of the scar region of interest (ROI) that is used for the colorimeter assessment. In order to ensure the same scar is being treated/assessed on each occasion, the scar will be identified and logged using clinical photography and skin markers, where present.

#### Exclusion criteria

Participant is **NOT** considered eligible for inclusion, if they are:

unable to give written informed consent.below 16 years of age.prone to keloid scarring by virtue of either a personal or family history.

Children aged 16 – 18 are able to participate with appropriate consent. Children under 16 would require the added risk of general anaesthesia^
59
^. Keloids are different to hypertrophic scars and show only a minimal response to PDL treatment^
60
^.

#### Other considerations

Darker Fitzpatrick skin types (V-VI) with more melanin may reduce effectiveness of the treatment and increase risk of adverse effects, such as permanent pigmentation changes^
61
^. They will be included in the trial, but extra information will be made available in the consent process concerning this increased risk. Precautions would be afforded for laser treatment by increasing the pulse duration. Their inclusion will increase global generalisability and recent literature shows good results for these skin types^
45,62
^. Patients with difficulty in understanding English will be provided with translator services.

### Sample size

No published data was found on the Minimal Clinically Important Difference for POSAS. A service evaluation study at Salisbury NHS Trust, on 15 patients treated with PDL, showed a change in the patient-rated POSAS from a mean (SD) of 35.8 (10.6) at baseline to 25.7 (11.2) at 12 months. A study in Holland on the effectiveness of silicone treatment on 46 scars from 23 patients showed mean (SD) pre-treatment scores of 31.0 (7.8) and post-treatment scores of 17.4 (11.5)^
63
^. The mean improvement at 12 months was 10.1 in Salisbury and 13.6 in Holland, and pooled over both studies and time-points the SD was around 10. A one-point improvement on each of the 6 items would equate to an overall change of 6 points over the duration of the study of 6 months, which constitutes 11% of the range of the scale (minimum 6, maximum 60). The PPI group felt that a change of 6 points represented an important improvement in scar quality.

A 1:1 allocation ratio is chosen. This design would require 60 participants in the control arm and 60 in the treatment arm to give 90% power; assuming a 2-sided 5% significance level, standard deviation of 10 and effect size of 6. This gives a total of 120 participants and, allowing for 20% drop out, implies recruitment of 150 participants.

This recruitment of 150 patients over 21 months across 7 centres represents 1 per centre per month and is similar to that identified for adults in the PEGASUS trial^
53
^. This sample size calculation does not take into account adjustment for baseline POSAS in the analysis. The PEGASUS study found a correlation of 0.545 between baseline and 6 month follow-up POSAS scores^
53
^. Taking into account a similar correlation in our study of 150 participants would imply that effect size of 5 (standardised effect size of 0.5) could be detected with 90% power.

The patient-rated POSAS has been chosen as the primary outcome in preference to the observer rated POSAS. The observerrated POSAS data, scaled similarly, collected in Salisbury and Holland gave a pooled SD of 6.7. For this secondary outcome measure, for which the rater would be blinded as to treatment allocation, the study will have over 99% power to detect a difference of 6 or more between trial arms.

### Recruitment

The study will recruit study participants across 7 sites, with the support of Clinical Research Network (CRN) funded research nurses. The involvement of the CRN research nurses may vary from site to site. For example, a site where CRN research nurses are already screening, approaching and consenting burns patients are very likely to ask the research nurses to screen, approach and consent patients into this study too. A site that is not research active may ask for research nurse support for these activities. Or, alternatively, the PI for that site may feel that, because they see the patients anyway, it is easiest for the PI to screen, approach and consent. The authors acknowledge that there will be a mix of approaches.

Each recruit is allocated a unique code that pseudonymises their data. At each visit, the identification of the participant is verified.

#### Recruitment feasibility

An online feasibility survey conducted by the CI showed that each study centre treats 30 – 80 patients per year that are eligible for recruitment and fulfil the study criteria. Audits of scar clinic attendance for 2018 show the total possible participants (Table 1).

This amounts to approximately 621 potential recruits across 7 sites; and with additional sites, if recruitment rate is low, 790 potential recruits across the 9 sites during the 21 month recruitment period. This translates to a recruitment rate of 24% and 19%, respectively, to get the target of 150 recruits.

The uptake to this study, as well as a reduced dropout rate, is favourable for the following reasons:

Participants are within an NHS pathway with no extra hospital visits required.Study design reduces participant burden by predominantly using outcome measures routinely collected.PDL treatment is quick and performed as an outpatient.PPI group suggested that patients are willing to try new treatment regimens to improve the scar.Participants in the control arm would still be offered an option of PDL treatment at the standard time-point of 6 months after randomisation. This would also apply to patients who do not opt into the study.

Recruitment will be reviewed by the Trial Management Group monthly meetings and Trial Steering Committee meetings at approximately 4, 8, 12 & 16 months into the recruitment phase. If recruitment numbers are low, the additional sites may be activated in a change to the protocol.

### Allocation

#### Sequence generation

Allocation will be determined using a validated password-protected web-based system hosted by the UKCRC registered Clinical Trials Unit (ExeCTU). Randomisation ratio is 1:1 control to treatment and is stratified by study site. The system uses random permuted blocks of varying size, within strata with possible block sizes of 2, 4 or 6.

#### Concealment mechanism

At first visit, data required for randomisation is entered onto the system. Blinded personnel may enter data for randomisation as the allocation is not displayed on the screen and is only transmitted by e-mail to those specified. The treating healthcare professional will be informed of patient treatment allocation by the CTU via email to their @nhs. net account. The principal investigator at that site will be copied in to this email defining the allocation. Blinded personnel entering data will not receive this e-mail, but will be informed by the system that the randomisation has been successful and that the e-mail has been sent.

#### Implementation

Randomisation can be performed by all site staff as the result is not displayed to the person inputting the data. The site staff can randomise participants in any order. However, it is expected that it will be done sequentially in chronological order of participant recruitment. A screening log will be collected at site recording all participants that were either recruited or were screened, but were not deemed eligible and why. Details of screening fails will not be entered on the web-based system, but will be collated for the Consolidated Standards of Reporting Trials (CONSORT) Statement. The allocation list will be stored by CTU and access to this list will be managed so that it is not shared with those enrolling and assigning participants.

### Participant timeline

Each participant attends the site for assessment at four study sessions and the primary end-point is at 6 months follow-up (Table 2).

#### Baseline data

Participant demographic data will be collected at baseline. Skin type will use the standard sixteen group classification of ethnicity currently used in the NHS; in addition to the Fitzpatrick scale. Age and sex will be collected. Additionally the following will be recorded: the depth of burn (superficial, superficial dermal (superficial partial), deep dermal (deep partial), full thickness or mixed); anatomical location; Total Burn Surface Area; aetiology of the burn injury; and time taken to heal for the wound selected for inclusion to the study. These data are all known to affect the likelihood of scarring.

### Outcomes

#### Primary outcome

Scar Quality - Patient-rated Patient Observer Scar Assessment Scale (POSAS version 2) score at 6 months (mean change from baseline).

#### Secondary outcome

Scar Quality: Observer-rated (blinded to treatment allocation) POSAS score at 6 weeks, 12 weeks and 6 months Scar Quality: Patient-rated POSAS score at 6 weeks and 12 weeksQuality of Life (QoL) - CARe scale with 14 subscalesIncremental cost per Quality Adjusted Life Years (QALY) over 6 months – calculated using Short form Health Survey (SF-12)Healthcare resource use over 6 month follow-up.Scar Redness – Erythema index (0-100) measured by Colorimeter (DSMIII ColorMeter, Cortex Technology, Denmark) at 6 months.Patient’s perception of change from baseline at 6 months - A 7-point scale question evaluates the overall improvement at the primary end-point, as judged by the participant.

#### Outcome measures

Scar quality and all measures and questionnaires assessed by the patient is for the study scar as a whole. Additionally, Observer POSAS will be performed for the study scar as a whole. Only the colorimeter measurement is carried out for the Scar ROI.

Burn scar quality is assessed using POSAS^
64
^; the most commonly used scar assessment scale^
65
^ and the only one including the patient’s perception of the scarring. POSAS v2.0 has been shown to be a reliable and feasible tool for the evaluation of scars^
66,67
^. It consists of two parts: a Patient Scale and an Observer Scale. Both scales contain six items that are scored numerically on a ten-step scale (1 – 10). Each makes up a ‘Total Score’, which ranges from 6 – 60 where a higher score reflects reduced scar quality. The mean POSAS scores for scar quality at the primary endpoint of 6 months are compared between trial arms. A reduction in the POSAS score determines whether the proposed intervention improves the scar quality.

The impact on the scarring on the psychological well-being of the patient is assessed using the CARe scale^
68
^. The Adult Scale consists of 53 items which cover 14 individual scales; 12 of which fulfilled Rasch and traditional psychometric analyses. These will be analysed in accordance with guidance provided by the CARe team.

QoL is further assessed by SF-12 in order to calculate Quality Adjusted Life Years (QALY). The SF-12 is a multi-purpose short form version of the SF-36 and s a generic measure of health status. The SF-12 physical (PCS-12) is scored using norm-based methods. The scale is transformed to have a mean of 50 and standard deviation of 10.

The resource implications of PDL will be captured in two ways. Secondary care resource use (e.g. clinic visits, resource requirements for PDL delivery) will be collected using a pro forma within the trial case report form (CRF). Primary care resource use (e.g. GP visits) and additional personal expenditures (e.g. burn care products, travel) will be collected using a patient completed questionnaire. This will be based on questionnaires used in previous clinical trials and adapted for the specific study requirements. Secondary care resource use is collected from routine clinic data. Wider costs, such as primary and social care resource use, are collected using direct patient self-reports. Patient-incurred costs are collected at baseline and follow-up.

As the proposed mechanism of PDL is the destruction of microvessels within the scar, an objective measurement of vascularity, or redness, is included. Scar colour is measured using the colorimeter (DSM III, Cortex, Denmark), which is a feasible tool that has been validated for the measurement of HBS^
69
^. It is important to measure the normal skin to account both for genetic differences between patients and environmentally-related changes in fixed pigmentation (e.g. tanning).

The patient’s perception of change question may correlate any differences seen in scar quality against the overall opinion of the improvement seen by the patient and/or clinician at the primary end-point. It will use a 7-point scale from considerably worse to considerably better. The question is, “What do you think is the overall change to your scar?”

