#### Data collection methods

##### Scar assessment

At each assessment, the participant acclimatises for at least 20 minutes to allow blood flow and skin temperature to equilibrate. The participant remains seated for the duration of assessment. Where the participant has multiple, non-contiguous scars at different anatomical locations, the “worst” scar, as identified by the participant, is assessed and included in the study. It would be prudent to be mindful to avoid areas where they may be a future need for surgery such as areas where contractures are beginning to form.

Whichever treatment group the patient is assigned to, each time they return for assessment, **the same area of hypertrophic scarring must be assessed and treated.** This will be known as the ‘Study Scar’. The ‘Study Scar’ is the scar that the patient, and the designated research team member at weeks 0 and 26, must assess and consider for all their visits. It is important that the participant is aware of this.

The ‘Study Scar’ and each ROI must be selected at the enrolment appointment. Firstly, the scar to be treated and assessed must be identified as a whole; this will be known as the ‘Study Scar’. This will be chosen in agreement with the participant. Where the participant has multiple, non-contiguous scars at different anatomical locations, the ‘Study Scar’ is agreed and included in the study. It would be prudent to be mindful to avoid any area for the ‘Study Scar’ where they may be a future need for surgery such as areas where contractures are beginning to form. The ‘Study Scar’ can be up to about 200 cm^
2
^ in size. This limit has been determined as the conventional total area of burn scar that would normally be treated by laser in one visit. Regardless of study group, the limit or guidance for size of ‘Study Scar’ area is the same.

Only part of this hypertrophic scar must then be selected as the ‘Scar ROI’. This should be the part of the burn scar that is the **
*most problematic to the participant.*
** This is typically excessively red, thickened and firm to touch compared to normal, unburnt skin. An area 4 cm x 4 cm is the optimal size for selection. This will the scar region of interest or ‘Scar ROI’ and this is the area that will be used for the **ColorMeter measurements only**.

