##### Economic analysis

There is paucity of economic evidence for burn scar treatment. A within-trial economic evaluation is conducted to assess the cost-effectiveness of PDL. The primary analysis is cost-utility analysis from NHS and Personal Social Services perspective. An incremental analysis will compare the differences in costs and Quality Adjusted Life Years (QALY) between SoC and PDL. An exploratory analysis using a societal perspective is performed to capture broader impacts of burns treatment. The SF-6D algorithm is applied to calculate QALY gained^
73
^. The economic evaluation follows best-practice guidelines.

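### The rule that patient questionnaires are answered for the study scar, as worded, also covers the SF-12, which the plan needs as a whole-person measure for its QALYs

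*Protocol article*

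**What the plan says.** The Outcome measures section sets the frame of reference for everything the patient completes: "Scar quality and all measures and questionnaires assessed by the patient is for the study scar as a whole". It then applies the same whole-scar rule to the observer POSAS and ends the contrast with "Only the colorimeter measurement is carried out for the Scar ROI".

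Further down, the same section describes the SF-12 as "a generic measure of health status" and adds: "The SF-12 physical (PCS-12) is scored using norm-based methods", on a scale with mean 50 and SD 10. It presents CARe as the measure of what scarring does to psychological well-being.

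The Scar assessment section defines the study scar as the one that the patient and the designated research team member "must assess and consider for all their visits. It is important that the participant is aware of this". The QoL and economic evaluation section then has the participant go on to CARe, the SF-12 and the resource-use questionnaires.

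The Economic analysis section makes cost-utility from the NHS and Personal Social Services perspective the primary economic analysis and states: "The SF-6D algorithm is applied to calculate QALY gained".

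**The concern.** QALYs built from the SF-6D assume that the respondent has described their health as a whole. The norm-based SF-12 score assumes the same. An answer confined to one scar, of at most about 200 cm², has neither meaning.

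The protocol thus gives the SF-12 a frame of reference in one sentence and, in the same section and the Economic analysis section, a use that this frame does not support. Cost-effectiveness is part of the stated research question, and incremental cost per QALY is a listed secondary outcome. The SF-12 is collected only at baseline and 6 months, and answers given under the wrong frame could not be repaired in the analysis.

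The Data management section allows research nurses, principal investigators or scar-management staff to collect data, with variation between sites. Some participants could therefore be steered to the scar while others follow the questionnaire's own wording.

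**Working it through.** No figure in the plan tests this point. The sample size (60 per arm, 120 in total, 150 after 20% dropout) rests on patient POSAS. It reproduces (59 per arm by the normal approximation for a difference of 6, SD 10, two-sided 5%, 90% power; 120/0.8 = 150) and does not depend on the SF-12. The check is therefore mainly a comparison of statements.

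**1. Reach of the sentence.** Scar quality is named first, and patient POSAS is the patient's scar-quality measure. The words that follow must therefore reach beyond POSAS. The other patient-completed items are the perception-of-change question, CARe, the SF-12 and the resource-use questionnaire. Nothing in the article exempts any of them.

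**2. Fit of each instrument to a one-scar frame.**
- Patient POSAS: fits.
- Perception of change: fits, since the question is about the scar.
- CARe: described as measuring the impact of scarring, so there is no conflict with its stated purpose. The only open matter is one scar versus all scarring.
- SF-12: conflicts with its description as generic, with its norm-based scoring and with its use for QALYs.
- Resource use: adapted to the study. The frame should follow the costing perspective, which the sentence does not mention.

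**3. How far a scar answer can depart from a whole-health answer.** Eligibility requires burns above 1% of body surface and states no upper limit. It provides for patients with several scars, of which one is chosen. The article does not say how many participants will have other scars or other burn effects, so the share affected is unknown. Eligibility criteria and Interventions also contradict each other on whether other scars may receive laser during the study. These statements must be reconciled, because they bear on how far the study scar and the whole patient can diverge.

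**4. Direction.** This is an illustration with assumed values, used for sign only. Let d be the whole-health utility difference at 26 weeks (PDL minus standard care) and k an assumed factor by which a scar-only frame scales it. With equal baselines and a linear change over half a year:

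QALY difference = 0.5 × 0.5 × d × k = 0.25 × d × k

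| d | k = 1 | k = 1.5 | k = 2 |
|---|---|---|---|
| +0.02 | 0.0050 | 0.0075 | 0.0100 |
| 0 | 0 | 0 | 0 |
| −0.02 | −0.0050 | −0.0075 | −0.0100 |

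Under this model a frame shared by both arms enlarges a difference that is already there. It creates none when the effect is zero, and it works against PDL when the effect is harmful.

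**The case against.** The strongest reply is that the sentence concerns the area assessed, not how health is framed. It opens a run of three statements that give the whole scar to the patient and observer ratings and the small region to the colorimeter alone. The instruction about all visits stands under the heading Scar assessment and is about returning to the same scar. The SF-12 and CARe have their own section, which carries no scar-only instruction. Nothing says that their items or instructions are reworded, CARe is to be analysed under its developers' guidance, and the economic evaluation is said to follow best practice. The forms and site procedures, which would settle the matter, are not shown.

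Most of this stands. It makes loose wording the likely explanation and rules out calling the SF-12 data invalid as a matter of fact. It does not remove the conflict: the sentence says all questionnaires, no text exempts the SF-12, and staff may work from the text as written.

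A reader might also infer that CARe is invalidated. The documents do not support that, since they present it as a scar-impact measure.

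**Conclusion.** The point holds for the SF-12 as a conflict between the literal rule and the instrument's stated use. If the rule is followed as written, the SF-6D values are not whole-person utilities, framing may be inconsistent, and the QALY comparison may be distorted. This depends on how sites present the form, which the article does not show.

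A reader might infer that the cost-utility result is tilted towards PDL, or that QALY gains are inflated by some multiple. Neither is established:
- The frame is common to both arms and, on the model above, could only enlarge a real or perceived difference.
- The documents contain no utilities from which a scaling factor could be derived.
- If other health problems act roughly additively and are untouched by treatment, randomisation balances them on average, and the factor could be close to 1 even in patients with many problems.
- A scar-only reading of the resource-use questionnaire would also change costs, in an unknown direction.

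The size is therefore unknown and the direction conditional. The correction is minor to moderate and confined to a secondary, economic outcome. The primary outcome is unaffected.

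**What to change.** Replace the sentence under Outcome measures with wording such as: *Patient POSAS and the perception-of-change question are answered for the study scar as a whole. The SF-12 is completed for the participant's overall health under its own standard instructions, CARe under its developers' guidance, and the resource-use questionnaire under the stated NHS and Personal Social Services costing perspective.* Limit the matching instruction to patients under Scar assessment to the same two scar-specific measures, and carry the line into the site procedures and the CRF.

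The cost is a sentence or two in each document, handled as an ordinary amendment. The article puts recruitment as imminent in November 2021, so at that point the change could have been made before any SF-12 was collected. Sample size, visit schedule and primary analysis do not change.
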